# STATISTICAL CONSIDERATIONS

1. **Sample Size Calculation**

Prior to the initiation of studies to identify the genetic determinants of a disease phenotypic, it is essential to first estimate that fraction of the phenotypic variation due to genetic factors. A commonly employed design to perform such an analysis is the collection of sibling pairs with the goal of estimating the heritability of the phenotype of interest. The COHORT sample will recruit multiple members from a family and through the collection of family history information, will be able to establish the biological relationship among individuals and use this information for genetic analyses. Siblings are typically employed for heritability studies since they are closely related and are expected to share, on average, half their genetic material. Studies in COHORT will focus on estimating the heritability of a number of different quantitative phenotypes including the age of onset of disease and the rate of disease progression (as measured by a number of different quantitative traits). In addition, with the collection of a number of novel biomarkers, COHORT is uniquely positioned to estimate the heritability of these biomarkers to determine whether genes are important predictors of their variability. For those phenotypes and traits, which are heritable, the collection of family data as part of COHORT will allow us to initiate studies to identify the genes and polymorphisms contributing to trait variability.

Broad-sense heritability (H2) is estimated as twice the sibling intraclass correlation, according to the method of Falconer (1989).  As shown below, for a phenotypic trait with 50% heritability (i.e. half the phenotypic variation is due to genetic effects), a sample of approximately 100 sibling pairs will have 80% power (with alpha=0.05). As the genetic contribution to the trait decreases, the required sample size increases. For a trait with only 20% heritability, a sample of approximately 600 sibling pairs is required for 80% power.

Falconer DS. 1989. *Introduction to Quantitative Genetics.* 3rd ed. Essex, England: Longman Scientific and Technical.

The COHORT study was designed to assemble a large descriptive database that will provide the opportunity to study many different factors potentially associated with HD-related events. Some potential factors include history of smoking, current concomitant medication use, or an unknown gene possibly associated with a predisposition to HD. The primary outcome for those affected with HD is progression of disease, which is measured by a decrease in total functional capacity (captured on the UHDRS 99). The primary outcome for those at risk would be phenoconversion or clinical onset of disease.

The table below gives the numbers of events required to detect an increase in risk corresponding to a hazard ratio of the specified magnitude associated with a single risk factor with the specified prevalence. A two-sided alpha level of 5% is assumed. The numbers of events given are for 80% power; for 90% power multiply all entries by 1.34.

| **Risk Factor Prevalence** | **Hazard Ratio** | | | | | | | |
| --- | --- | --- | --- | --- | --- | --- | --- | --- |
| **5.0** | **4.0** | **3.0** | **2.5** | **2.0** | **1.8** | **1.6** | **1.5** |
| **1%** | 306 | 412 | 656 | 943 | --- | --- | --- | --- |
| **2%** | ***154*** | ***208*** | 331 | 476 | 833 | --- | --- | --- |
| **3%** | ***104*** | ***140*** | 223 | 321 | 561 | 780 | --- | --- |
| **4%** | ***79*** | ***106*** | ***169*** | 243 | 425 | 591 | 924 | --- |
| **5%** | ***64*** | ***86*** | ***137*** | ***197*** | 344 | 478 | 747 | --- |
| **6%** | ***54*** | ***72*** | ***115*** | ***166*** | 289 | 402 | 629 | 846 |
| **8%** | ***41*** | ***55*** | ***88*** | ***127*** | 222 | 308 | 482 | 648 |
| **10%** | ***34*** | ***45*** | ***72*** | ***104*** | ***181*** | 252 | 394 | 530 |
| **12%** | ***29*** | ***39*** | ***62*** | ***88*** | ***155*** | ***215*** | 336 | 452 |
| **14%** | ***25*** | ***34*** | ***54*** | ***78*** | ***136*** | ***188*** | 295 | 396 |
| **16%** | ***23*** | ***30*** | ***48*** | ***69*** | ***121*** | ***169*** | 264 | 355 |
| **18%** | ***21*** | ***28*** | ***44*** | ***63*** | ***111*** | ***154*** | 240 | 323 |
| **20%** | ***19*** | ***25*** | ***41*** | ***58*** | ***102*** | ***142*** | 222 | 298 |
| **25%** | ***16*** | ***22*** | ***35*** | ***50*** | ***87*** | ***121*** | ***189*** | 254 |
| **30%** | ***14*** | ***19*** | ***31*** | ***44*** | ***78*** | ***108*** | ***169*** | 227 |
| **35%** | ***13*** | ***18*** | ***29*** | ***41*** | ***72*** | ***100*** | ***156*** | ***210*** |
| **40%** | ***13*** | ***17*** | ***27*** | ***39*** | ***68*** | ***95*** | ***148*** | ***199*** |
| **45%** | ***12*** | ***16*** | ***26*** | ***38*** | ***66*** | ***92*** | ***143*** | ***193*** |
| **50%** | ***12*** | ***16*** | ***26*** | ***37*** | ***65*** | ***91*** | ***142*** | ***191*** |

Suppose we are interested in a risk factor with a prevalence of 10%. We would like to know how much greater the risk of a relevant phenotypic event (e.g., progression of HD or phenoconversion) is for those with the risk factor compared to those without the risk factor. If we want to be 80% sure to detect a hazard ratio of at least 2.0 (e.g., double the risk), we would need 181 subjects to reach that event (e.g., phenoconvert). If we want to be 90% sure, we would need 181 X 1.34=243 subjects to reach that event.

The above hazard ratio table shows that if 220 subjects phenoconvert, we will have good power to detect substantial effects (hazard ratio exceeding 2.0 –) of the risk factor assuming that is they are not too rare in the study population (bold). For example, assuming that history of smoking is prevalent in the study population, we should be able to detect the increased risk in phenoconversion due to history of smoking.

Only those subjects in COHORT who are unaffected HD gene carriers are at risk to phenoconvert. In theory, this population will include all unaffected subjects who are known to carry the HD gene (as a result of pre-symptomatic DNA testing) and about 40% of the unaffected subjects with a HD parent who do not know their gene status (chose not to undergo DNA testing) but are expected by probability to carry the HD gene. As more of these subjects are enrolled and followed to phenoconversion, COHORT will have increasing power to detect genetic polymorphisms or other factors that influence the clinical onset of HD.

The NIH-sponsored prospective studies “Neurobiological Predictors of Huntington’s Disease” (Predict-HD - that is examining phenotype among unaffected subjects who are known to carry the HD gene as a result of presymptomatic DNA testing), and “Prospective Huntington’s at Risk Observational Study (PHAROS - that is examining phenotype among unaffected subjects with a HD parent who have unknown gene status having chosen not to undergo DNA testing) will in the coming years provide increasingly accurate estimates of phenoconversion, including the sensitivity and specificity of this therapeutically relevant phenotype. COHORT will also provide an ongoing observational study for interested and eligible subjects who were not able to participate in Predict-HD or PHAROS as well as for subjects who conclude their research participation in Predict-HD and PHAROS.

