| **Sample Size Considerations** | In performing an observational cohort study, the larger the sample size used for data analysis, the more applicable the results are to the population as a whole. Therefore, COHORT will allow each site to enroll as many subjects as are eligible and willing to participate. Several genetic studies are proposed to delineate the genetic and environmental effects on relevant phenotypic events such as phenoconversion or development of signs of HD. Initial analyses will estimate the proportion of phenotypic variation due to genetic factors and will be followed by studies designed to identify the DNA sequence changes that underlie the phenotypic variation. To estimate the influence of genetic factors, typically samples of 500-1,000 sibling pairs are required to detect genetic contributions of as little as 20%. This would typically be considered the lower bound for a covariate that might be identified, which could act as a meaningful covariate for therapeutic trials aimed at delaying the phenotypic event (e.g., HD phenoconversion). To identify the genes and sequence variation underlying the trait, typically even larger samples are required, but they can include various types of related individuals such as siblings, half siblings, parent-offspring, cousins, etc. A sufficiently large sample size of a relevant phenotypic event (e.g., phenoconversion or development of signs of HD) will provide adequate statistical power to detect a relevant risk factor (e.g., genetic polymorphism or environmental effect) that influences the phenotypic event and that might meaningfully serve as a covariate for therapeutic trials aimed at delaying the phenotypic event (e.g., HD phenoconversion). |

Cooperative Huntington’s Disease Observational Research Trial **(COHORT)**

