COHORT is the centerpiece of the Huntington Project (<http://www.huntingtonproject.org/>), a worldwide collaborative undertaking to develop treatments that make a difference for HD. The Huntington Project and COHORT are sponsored by HP Therapeutics Foundation, Inc., a not-for-profit corporation that supports a variety of research projects seeking to find treatments for Huntington's disease. COHORT was planned and is overseen by the Huntington Study Group (HSG), (<http://www.huntington-study-group.org/>), a not-for-profit consortium of researchers established in 1993 to improve treatments for HD. The HSG now comprises more than 70 sites worldwide and has carried out 10 multi-center observational and interventional studies involving more than 10,000 individuals affected by HD. COHORT builds on the accrued HSG databases from these studies and its established network of investigators and research subjects.

HD is a uniformly progressive neurodegenerative disorder characterized clinically by movement disorder (typically chorea), behavioral disturbances, and cognitive impairment. The mean age of HD onset is approximately 39 years, after which illness progresses steadily over a period of 15-25 years. Approximately 30,000 people in the United States have clinical manifestations of HD, and an additional 150,000 unaffected individuals (about 60,000 HD gene carriers and 90,000 non-HD gene carriers) are immediately at risk to develop HD. In the United States, only about 5-10% of individuals at immediate risk for HD have chosen to undergo pre-symptomatic DNA testing to learn if they carry the HD gene.

The steady worsening of the motor, cognitive, and behavioral features of HD results in progressive functional decline. Clinical rating scales that chart the progression of illness have been widely used to establish the rate of functional decline in a variety of HD populations.[[18]](#endnote-19),[[19]](#endnote-20),[[20]](#endnote-21),[[21]](#endnote-22),[[22]](#endnote-23),[[23]](#endnote-24) The extent of functional disability correlates well with the extent of basal ganglia degeneration detected by neuroimaging and postmortem examination.Error: Reference source not found,[[24]](#endnote-25),[[25]](#endnote-26),[[26]](#endnote-27),[[27]](#endnote-28)

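### Age at onset is listed for heritability estimation as twice the sibling intraclass correlation, which cannot score carriers not yet affected and is biased upward in the both-affected pairs that remain

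*Protocol*

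**What the plan says.** Protocol section VIII.a (Sample Size Calculation) describes the planned heritability work as "estimating the heritability of a number of different quantitative phenotypes including the age of onset of disease and the rate of disease progression". The only estimator it gives is that heritability "is estimated as twice the sibling intraclass correlation, according to the method of Falconer (1989"). The pair numbers rest on it: at 50% heritability "a sample of approximately 100 sibling pairs will have 80% power (with alpha=0.05"), and "For a trait with only 20% heritability, a sample of approximately 600 sibling pairs is required for 80% power". The Synopsis (Sample Size Considerations) says that "typically samples of 500-1,000 sibling pairs are required to detect genetic contributions of as little as 20" per cent, and calls this the lower bound for a useful covariate.

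Section II (Background and Rationale) gives about 30,000 affected people in the United States and, among unaffected people at immediate risk, "about 60,000 HD gene carriers and 90,000 non-HD gene carriers". It also states: "The mean age of HD onset is approximately 39 years, after which illness progresses steadily over a period of 15-25 years". Section III lists unaffected gene-positive people and unaffected at-risk people among the groups to be enrolled. Later in section VIII.a, phenoconversion is treated as an event, with power counted in events and hazard ratios. Section VIII.b leaves analytical methods to be determined.

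**The concern.** An intraclass correlation needs a value on both siblings. Age at onset is a time to event, and a carrier who has not phenoconverted has only a lower limit for it. Applied as stated, the estimator drops every pair with an unaffected carrier.

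The pairs that remain are not a neutral subset. Each onset must precede that sibling's current age. If both must also be alive, each onset must lie within about the last 15-25 years. With a 25-year course, living affected siblings aged 50 and 52 must have had onset at 25-50 and 27-52; siblings aged 70 and 72 must have had it at 45-70 and 47-72. Across pairs, the onsets move together because the ages do. This is separate from the shared CAG allele and from shared environment, and adjusting for CAG does not remove it.

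At stake are the reported genetic share of onset variation and the meaning of the 100 and 600 pair figures for this trait.

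**Working it through.** **1. The protocol's own figures.** Fisher z test of zero correlation: n = ((z_alpha + z_power) / atanh(H2/2))^2 + 1.5.
- H2 = 0.50, one-sided 5%: ((1.645 + 0.842) / 0.2554)^2 + 1.5 = 96.3, so 97 pairs (stated: about 100).
- H2 = 0.20, one-sided 5%: (2.486 / 0.1003)^2 + 1.5 = 615.6, so 616 pairs (stated: about 600).
- Two-sided 5% gives 122 and 782. The stated numbers therefore fit a one-sided test on a correlation observed in every pair.

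**2. Carriers without an onset age.** From section II: 60,000 / (30,000 + 60,000) = 67% of US carriers. If siblings were affected independently, (1/3)^2 = 11% of carrier pairs could be scored. The simulations in step 4 with 58-73% of carriers unaffected gave 11-23%.

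**3. Apparent heritability when the truth is zero.** Monte Carlo of carrier sibling pairs.
- From the protocol: mean onset 39; course 15-25 years; CAG explaining 65% of onset variance (the middle of its 60-70%).
- Assumed, because the protocol gives no figure: onset SD 12 years; sibling age-gap SD 4 years; the same CAG in both siblings, fully adjusted; current age uniform over 18-80, or over 18-50, where about 64% of living carriers are unaffected.
- Residual onset is independent between siblings. Score = 2 x intraclass correlation of the CAG-adjusted onset in pairs with both onsets observed.

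| Follow-up (years) | Living pairs, 18-80 | Living pairs, 18-50 | Deceased siblings' onsets also used, 18-80 | Deceased siblings' onsets also used, 18-50 |
|---|---|---|---|---|
| 0 | 0.65 | 0.47 | 0.08 | 0.16 |
| 5 | 0.49 | 0.33 | 0.07 | 0.13 |
| 10 | 0.36 | 0.23 | 0.06 | 0.10 |
| 20 | 0.20 | 0.10 | 0.03 | 0.05 |

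For living pairs aged 18-80, the scoreable share is 32%, 46%, 59% and 81% at 0, 5, 10 and 20 years. The 5% F test falsely rejects in 96%, 80%, 55% and 25% of samples of 100 pairs, and in 100%, 100%, 99.9% and 79% of samples of 600.

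**4. Controls and sensitivity (no CAG term, onset SD 8-15, true value zero).**
- All onsets known: 0.00. Both-affected pairs with unrelated current ages: 0.00. The cause is truncation combined with similar ages.
- Age ranges with 58-73% of carriers unaffected, living pairs at baseline: 0.37-0.94 for age-gap SD 3, 0.24-0.82 for SD 5, 0.04-0.58 for SD 8. With truncation at current age only: 0.24-0.29, 0.18-0.25 and 0.04-0.18.
- True heritability 0.50 (age-gap SD 5, onset SD 10-12), living pairs: 0.75-1.32, partly above the possible maximum of 1.

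**5. Current age as a linear covariate** (model of step 3, living pairs). The false value falls to about 0.01-0.03, but a true 0.50 then reads as about 0.25.

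**The case against.** **The method is not fixed.** The estimator stands in a sample size section, and section VIII.b leaves methods open. The planners plainly saw onset as an event, since the hazard-ratio table treats it so. This stands in part: the choice can still be changed. But section VIII.a names the trait, states one estimator and derives the pair numbers from it, and section VIII.b does not withdraw that.

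**Survival truncation may not apply.** The Family History Questionnaire asks for dates of death and for age at diagnosis of affected relatives, and section II says that family history will help to assess heritability. This stands, and it brings the artefact down to about 0.03-0.16. However, the questionnaire is optional, section VI describes its use as identifying and linking families, and CAG is genotyped only in enrolled adults. The 0.03-0.16 range treats CAG as known for deceased siblings too. Truncation at current age remains in any case.

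**A routine age covariate removes the false positive.** True, but it halves a real effect, and the protocol states no such adjustment.

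**Stronger readings a reader might infer.**
- That two-thirds of enrolled carriers have no onset age: the figure describes US carriers, and clinic recruitment may change the mix.
- That the test rejects almost always under the null: at 100 pairs this holds for baseline scoring of living pairs, but the rate falls to 55% and 25% at 10 and 20 years, and section III sets no end date.
- That gene-finding on onset depends on this estimate: section VIII.a does order the work that way, but section II already reports residual onset variation as strongly heritable and cites a linkage scan.

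**Conclusion.** The defect holds: for age at onset, the stated estimator cannot use carriers without onset, and it is biased upward in the both-affected pairs that it can use. The direction was upward in every scenario without adjustment for current age. The size is not determined by the protocol, which gives no onset SD, sibling age gap or enrolled age mix. Under the step 3 assumptions it ranges from small (0.03-0.16, deceased siblings included) through about 0.1-0.5 (living pairs, 5-20 years of follow-up) to about 0.45-0.65 (living pairs at baseline). It can therefore reach or exceed the protocol's 20% lower bound, but a large false heritability is not certain. The 100 and 600 pair figures are sound arithmetic for a trait measured on both siblings; they do not carry over to age at onset.

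**What to change.** In section VIII.a:
- Remove age at onset from the traits estimated as twice the sibling intraclass correlation.
- State that its familial aggregation will be estimated with a survival model for related carriers (for example shared frailty) that includes CAG, treats unaffected carriers as censored at their last visit, and accounts for age at entry and survival to enrolment. The exact model can be left to the analysis plan.
- State that the 100 and 600 pair figures apply only to traits measured on both siblings, and that power for onset depends on the number of observed onsets.

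The cost is a later and less precise onset estimate, and pair numbers that no longer cover onset. The data needed (research CAG genotype, visit dates, phenoconversion) are already collected, so no subjects or procedures are added.

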**Cooperative Huntington’s Disease Observational Research Trial (COHORT)**

# STUDY OBJECTIVE

##### COHORT (Cooperative Huntington Observational Research Trial) is a coordinated research effort by Huntington Study Group research centers worldwide to prospectively collect data from consenting individuals who are affected by Huntington’s disease (HD) and who are part of an HD family. The systematically accrued data from annual prospective assessments will relate clinical characteristics (phenotypes) between families with genetic and environmental factors. The knowledge from these relationships will better inform us about the onset and progression of HD, help identify potential interventions for HD, and aid in planning research studies of experimental treatments aimed at slowing or postponing the onset of HD. The consented collection of biological samples will further provide research material and correlative data for scientists to identify biomarkers that parallel the development and progression of HD. Identification of biomarkers will in turn contribute to our understanding of HD and enhance the efficiency and power of disease-modifying therapeutic trials.

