# CHARACTERISTICS OF THE RESEARCH POPULATION

- 1. **Number of Subjects**

This study will include as many subjects who are eligible and willing to participate. We expect that thousands of individuals may participate.

- 1. **Gender of Subjects**

Both males and females will be included in this study.

- 1. **Age of Subjects**

Individuals 18 years of age and older will be asked to participate in all aspects of the study. For individuals under the age of 18, only those with clinically diagnosed features of HD in the setting of a confirmatory family history or clinically diagnosed features of HD with a positive gene test will be eligible to participate. Subjects under the age of 18 will only participate in the phenotypic evaluation, which includes medical history, neurological and physical examination, and the UHDRS 99. It will be left up to the discretion of the site investigator to determine if a subject under the age of 18 is able to complete the cognitive assessment, functional assessment, independence scale, and functional capacity in the UHDRS 99.

If a child turns 18 while participating in COHORT, he or she will be required to provide written consent to continue participation in the study.

- 1. **Racial and Ethnic Origin**

There are no restrictions on ethnicity or race. Past experience in HD research has shown an underlying lower prevalence of HD in non-Caucasian populations, although there are no definite racial predispositions and the disease is found throughout the world.

- 1. **Inclusion Criteria**

For those 18 years of age and older, there are four different types of individuals who may be eligible to participate in COHORT:

1. An individual with clinically diagnosed features of HD in the setting of a confirmatory family history or an individual known to carry the HD gene as confirmed by DNA testing (individual is defined as the ‘proband’).
2. A first-degree relative (parents, siblings, or children) of an individual with clinically diagnosed features of HD in the setting of a confirmatory family history or of an individual known to carry the HD gene as confirmed by DNA testing.
3. A grandparent or grandchild of an individual participating in COHORT who meets criterion 1.
4. A HD family member who has no risk for HD due to no family history (spouses of proband only) or negative gene testing. This individual must have an affected or gene positive spouse or family member participating in COHORT to be included.

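### Heritability is set at twice the sibling correlation with no condition on HD carrier status, so for biomarkers measured in carriers and non-carriers alike it understates the genetic share it is meant to estimate

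*Protocol*

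**What the plan says.** Section VIII a) opens with the aim of estimating how much of a trait's variation is genetic, before any gene search begins. It then gives one estimator: "Broad-sense heritability (H2) is estimated as twice the sibling intraclass correlation". The named traits include age at onset, rate of progression and, as an addition, biomarkers: "COHORT is uniquely positioned to estimate the heritability of these biomarkers to determine whether genes are important predictors of their variability". Traits found heritable go on to gene identification.

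The pair counts rest on the same estimator. About 100 sibling pairs give 80% power at 50% heritability, and "For a trait with only 20% heritability, a sample of approximately 600 sibling pairs is required for 80% power". The synopsis gives a wider range for the 20% case: "typically samples of 500-1,000 sibling pairs are required to detect genetic contributions of as little as 20" percent.

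The heritability text says nothing about carrier status. Inclusion criterion 2 in section IV admits "A first-degree relative (parents, siblings, or children) of an individual with clinically diagnosed features of HD", whatever the relative's own gene status, and criterion 4 admits gene-negative family members. Repository specimens are offered to all adults (section VI b). The Study Objective says which biomarkers matter: the repository is meant to help scientists "identify biomarkers that parallel the development and progression of HD".

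**The concern.** Doubling the sibling correlation recovers a genetic share only if each contributing gene makes siblings more alike by half of its own variance share. The HD gene does not behave like that in these families. It is dominant, and families enter because someone in them carries it. Within a sibship with one heterozygous parent, one sibling's carrier status says nothing about the other's. If the pair is formed around a known carrier, status is negatively correlated within pairs.

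A biomarker, unlike age at onset, has a value in carriers and non-carriers alike. A difference between the two groups therefore enters the denominator of the intraclass correlation without a matching positive term in the numerator. The stronger the link to HD, the larger the shortfall. At stake are the reading of whether genes matter for a given biomarker, the choice of traits taken on to gene finding, and whether the stated pair counts apply.

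**Working it through.** **1. The plan's own figures.** Fisher z test of a sibling correlation t = H2/2 against 0: n = ((z_alpha + z_power)/atanh(t))² + 3.

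- H2 = 50%, t = 0.25: one-sided 5% gives 98 pairs; two-sided gives 124.
- H2 = 20%, t = 0.10: one-sided 5% gives 618 pairs; two-sided gives 783.

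The stated 100 and 600 are reproduced with a one-sided test, although the section does not state sidedness. Power at the stated numbers is 81% and 79%. One-sided 5% is used below.

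**2. Sibling correlation of carrier status (r).** C = carrier, N = non-carrier; p is the carrier frequency over all pair members.

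- Pairs reached through a carrier parent: CC 1/4, CN 1/2, NN 1/4. p = 0.5, covariance 0.25 - 0.25 = 0, r = 0.
- Carrier proband plus a sibling at 50% risk: CC 1/2, CN 1/2. p = 0.75, variance 0.1875, covariance 0.5 - 0.5625 = -0.0625, r = -1/3.
- Carrier proband plus a sibling at 40% risk (the protocol's figure for untested unaffected subjects with an HD parent): p = 0.7, variance 0.21, covariance 0.4 - 0.49 = -0.09, r = -0.43.
- Pairs required to contain at least one carrier: CC 1/3, CN 2/3, r = -1/2.
- Sibships of a proband's grandchildren (criterion 3), where the linking parent may be a non-carrier: p = 0.25, r = +1/3.

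**3. Effect on the estimator.** Let v be the share of biomarker variance due to carrier status and h the heritability of the remainder. Both are assumptions. Then

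2t = 2vr + (1 - v)h, while the total genetic share is v + (1 - v)h.

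For h = 50%:

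| v | Total genetic share | 2t, r = 0 | 2t, r = -1/3 | 2t, r = +1/3 |
|---|---|---|---|---|
| 10% | 55% | 45% | 38% | 52% |
| 30% | 65% | 35% | 15% | 55% |
| 50% | 75% | 25% | -8% | 58% |

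Example, v = 30% and r = -1/3: 2 × 0.30 × (-1/3) + 0.70 × 0.50 = -0.20 + 0.35 = 0.15.

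Every entry is below the total genetic share. The first two 2t columns are also below the residual 50%; the grandchild column is above it.

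**4. When the estimate turns negative.** With r = 0, 2t = (1 - v)h, which cannot be negative. With r = -1/3 it is negative when v > h/(h + 2/3), that is above 43% for h = 50% and above 23% for h = 20%. Writing d for the carrier difference in residual SDs, v = 0.1875d²/(1 + 0.1875d²), so these limits are d = 2.0 and d = 1.27. For pairs with at least one carrier they are 1.5 and 0.95.

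**5. Power at the stated pair counts.** Take d = 1.

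- h = 50%, 100 pairs: 2t is 0.40 (r = 0) or 0.32 (r = -1/3). Power falls from 81% to 64% or 47%.
- h = 20%, 600 pairs: 2t is 0.16 or 0.06. Power falls from 79% to 62% or 19%.

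**6. After adjustment.** With carrier status removed, or with both siblings carriers, 2t returns to 0.50 and 0.20, and 98 and 618 pairs again suffice. Simulation of 1,000,000 pairs under each of the first four pair types in step 2 agreed: adjusted 2t was 0.498-0.504 and 0.197-0.202.

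**The case against.** The best defence is that the section gives a generic estimator as the basis for a sample size. It does not say that raw biomarker values from mixed pairs will be analysed. The Data Analysis section leaves methods to the study group, every adult is CAG-genotyped, and the background describes the genetic aim as finding modifiers beyond CAG length. A later plan could restrict or adjust the pairs at no loss. The display that should support the pair counts is also not in the available text, so its assumptions cannot be seen.

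This lowers the importance of the point but does not remove it. The section states an estimator, a target (the genetic share of trait variation) and pair counts, and for a trait measured in both groups these three do not fit together. A later adjustment would estimate a different quantity from the one defined and powered here.

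Three points on scope stand in full:

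- A reader might infer that every sibship has one heterozygous parent. Criterion 3 contradicts this: grandchild sibships can have positive carrier correlation.
- The share v is assumed. The model also shifts all carriers equally. Stage of disease, or CAG length shared between carrier siblings, can add positive covariance and offset part of the bias.
- The primary outcomes, decline in functional capacity and phenoconversion, are untouched, and enrolment has no cap that depends on 100 or 600 pairs.

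**Conclusion.** The concern holds for traits measured in both carriers and non-carriers. Applied as written, the estimator falls below the total genetic share for every pair type examined, and below residual heritability for all except grandchild sibships. With residual heritability of 50%, it gives about 38-45% when carrier status explains 10% of variance and 15-35% when it explains 30%, against total genetic shares of 55% and 65%. These ranges span pairs with r = 0 to r = -1/3 and rest on an equal shift in all carriers.

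A reader might go further and conclude that HD-linked biomarkers will come out with negative or near-zero heritability. The documents do not support that as a general statement. It needs pairs selected through a carrier and a carrier effect of about 1-2 SD or more, and no effect size is given. Nor does the point reach age at onset or progression, which are defined in affected subjects only. It is a cheap correction to an analysis outside the primary outcomes, not a must-fix.

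**What to change.** In section VIII a), add that for any trait measured in both carriers and non-carriers the sibling correlation is computed after adjusting for carrier status, with CAG length and age as covariates, or within carrier-concordant pairs. Report the share of variance due to the HD gene on its own line. State that the 100 and 600 pair figures refer to this residual trait, and state the sidedness of the test behind them.

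The cost is a few sentences and slightly more analysis. Genotype and age are already collected for adults, so no visit or specimen changes. The downside is that two quantities are reported instead of one, and the adjusted figure means heritability beyond the HD gene. Restricting to concordant pairs also costs pairs: with proband-plus-sibling pairs at 50% sibling risk only half are concordant, so 98 usable pairs would need about 98/0.5 = 196 enrolled. Adjustment keeps them all.
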